**Table 1 T1:**
[figure not shown]
Evaluation of the treatment process.

The following conditions will be recorded at the end of the treatment (every 3 months during year 1–2, every 6 months thereafter):

1.Survival2.Physical condition based on the ECOG performance status score3.A physical examination4.Vital signs5.Electrocardiogram6.A barium meal7.Esophageal endoscopic biopsy (at the first follow-up time, and then at least once a year)8.CT scan for tumor evaluation (at the first follow-up time, and then at least once every 6 months).

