### Recruitment and study design

3.1

This trial is a prospective, randomized, multicenter phase II clinical trial. Patients with unresectable or medically unfit for surgery and no distant metastasis of esophageal squamous cell carcinoma will be randomized into 2 groups (Fig. 1): one group receiving S-1 concurrent intensity-modulated radiotherapy treatment (experimental group) and S-1 plus cisplatin concurrent intensity modulated radiation therapy (control group).

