### Assessment of the primary and secondary endpoints

3.5

In this trial, endoscopic complete response (CR) 3 months after completion of treatment will be evaluated as the primary endpoint. Endoscopic CR was defined as the complete disappearance of any tumor ulceration or stenosis with no new lesion (all endoscopic pictures and reports had to be available), observation of the entire esophagus as defined by Tahara et al,^[22]^ but also no CT-scan progression. Biopsies were not mandatory. Tumor responses were assessed during week 15 according to RECIST guidelines.^[23]^ The primary tumor was assessed on CT scan with measure of the vertical length and maximal thickness of the esophageal wall on transverse plane. Secondary endpoints are the toxicity, progression-free survival (PFS), and overall survival (OS). Adverse events will be encoded in accordance with the requirements of Med DRA. Severity of adverse events will be graded according to the NCI-CTC classification criteria. The toxicity of the treatment, including acute and chronic toxicity will continue to be evaluated during treatment and during follow-up (Table 1). Any serious adverse drug reactions will be reported promptly to the hospital ethics committee. An intent-to-treat analysis (on all randomized patients) was planned for all other end points. PFS was defined as the date from randomization to tumor progression or death. OS was measured from date of study entry to date of death.

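### CT and endoscopy have only a minimum frequency, counted from end of treatment, so PFS can be biased if examination rates or treatment end dates differ by arm

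*Protocol article*

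**What the plan says.** All of this is in section 3.5 of the Protocol article, in the endpoint text and in the follow-up list printed after Table 1.

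- PFS is secondary: "Secondary endpoints are the toxicity, progression-free survival (PFS), and overall survival (OS". Its time origin is randomization: "PFS was defined as the date from randomization to tumor progression or death".
- Follow-up hangs on a different date: "The following conditions will be recorded at the end of the treatment (every 3 months during year 1–2, every 6 months thereafter". One list serves both arms. It includes a physical examination and a barium meal.
- Two examinations have their own frequency: "CT scan for tumor evaluation (at the first follow-up time, and then at least once every 6 months" and "Esophageal endoscopic biopsy (at the first follow-up time, and then at least once a year". The text shown gives neither an upper limit nor a window.
- The primary endpoint is tied to treatment end: "endoscopic complete response (CR) 3 months after completion of treatment will be evaluated as the primary endpoint". Its definition also requires that CT shows no progression.

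Section 3.1 describes the design without mentioning masking: "This trial is a prospective, randomized, multicenter phase II clinical trial". Section 3.3 gives cisplatin to one arm only and differs between arms in the S-1 days during radiotherapy.

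**The concern.** Progression is dated when somebody looks and finds it. A minimum frequency allows one patient to be scanned every 3 months and the next every 6, both within the plan. If that choice follows the arm, the more closely watched arm appears to progress sooner with no difference in disease. Treatment looks identifiable to staff, so the choice could follow the arm.

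The anchor is a second route and needs no discretion by the site. If one arm stops treatment earlier or later, every later scan in that arm moves relative to randomization. The Introduction motivates the trial by poor tolerance of two-drug chemoradiotherapy, citing completion of planned treatment in only 9% to 38.5% of patients on 5-FU/cisplatin. Unequal treatment end dates are therefore plausible on the trial's own reasoning.

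At stake is the reading of PFS, which will be part of the evidence on whether S-1 alone has the same effect as the combination. A timing artefact could imitate a difference or hide one.

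**Working it through.** **Plan's own figure.** The plan states no PFS median, hazard ratio or event count, so there is none to reproduce. The total of 88 in section 3.6 is built on complete response. It enters here only as 88 / 2 = 44 per arm.

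**Is the anchor equal by plan?** Section 3.2 gives 30 to 33 fractions at 5 per week, which is 6.0 to 6.6 weeks. Section 3.3 gives both arms a 2-week gap and two 21-day cycles. The planned end is 6.0 + 2 + 6 = 14.0 to 6.6 + 2 + 6 = 14.6 weeks in both arms. The anchor differs only through delay or early stopping.

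**Simulation with no true difference.** The following are assumptions, not figures from the documents: exponential PFS with median 8, 12 or 18 months; 36 months of follow-up; treatment end at week 14.3; first scan 3 months later; scan dates scattered by about 1 week either way; progression dated to the next scan. Each case has 1,500 runs. The hazard ratio is the one-step log-rank estimate exp(U/V), where U is observed minus expected events in the first-named arm and V is its variance. The percentage is the share of runs with |z| > 1.96. Its Monte Carlo error near 5% is √(0.05 × 0.95 / 1500) ≈ 0.6 points.

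| Case | Median 8 | Median 12 | Median 18 |
|---|---|---|---|
| 6-monthly v 6-monthly | 1.00, 4.7% | 1.00, 5.9% | 1.02, 6.3% |
| 6-monthly v 3-monthly | 0.91, 7.7% | 0.90, 7.9% | 0.92, 6.3% |
| 6- v 3-monthly, half of progressions found between scans | 0.95, 5.4% | 0.95, 5.7% | 0.95, 6.9% |
| S-1 v control, both 6-monthly, 30% of control ends 8 weeks early | 0.96, 6.5% | 0.96, 4.7% | 0.97, 5.1% |
| The same with 60% | 0.91, 7.4% | 0.93, 6.7% | 0.93, 6.4% |
| 3-monthly v 3-monthly | 0.99, 5.5% | 0.99, 5.3% | 1.00, 5.0% |

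The 8 weeks in the early-stopping rows is the 2-week gap plus the two adjuvant cycles, that is, stopping when radiotherapy ends.

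The 6- v 3-monthly row is an extreme. It applies to every patient and keeps 3-monthly scanning for all 36 months, although visits become 6-monthly after year 2. Scatter matters too. With everyone examined on exactly the same days, the 3- v 6-monthly hazard ratio was 1.11 to 1.19, which inverts to 1/1.19 = 0.84 and 1/1.11 = 0.90. Tied dates inflate the effect in that version, and real visits do not tie so exactly.

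**Which date is treatment end?** The article does not say whether follow-up counts from the end of radiotherapy or of the adjuvant cycles. Taking 3 months as 13 weeks, the first follow-up falls at weeks 19.0 to 19.6 or 27.0 to 27.6. Neither matches "Tumor responses were assessed during week 15 according to RECIST guidelines".

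**The case against.** The strongest reply is that one list applies to both arms, so nothing is biased unless practice diverges by arm. That stands: the first row of the table shows no bias. A reader might infer from the wording that PFS in this trial is biased. The documents do not support this, and open-label conduct is itself an inference from the regimens and from silence on masking. The sign is also open. Early stopping in the control arm would favour S-1 alone, delays there would do the reverse, and either arm might attract closer scanning.

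A reader might also infer a large effect from PFS at one time point. Take an assumed median of 14 months, scans at 6.4, 9.4 and 12.4 months in one arm, and scans at 6.4 and 12.4 in the other. Apparent PFS at 12 months is then 2^(−9.4/14) = 0.628 v 2^(−6.4/14) = 0.728. This ten-point gap exists only because month 12 falls just before a shared scan. At 12.4 months both arms stand at 2^(−12.4/14) = 0.541. If follow-up counts from the end of radiotherapy, the scans fall at 4.5, 7.5 and 10.5 v 4.5 and 10.5 months, and the 12-month gap is zero. The gap should not be used as the measure of the problem.

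The distortion is further limited because deaths count as PFS events when they occur, and because the 3-monthly examination and barium meal are common to both arms. The drop-out rule for toxicity delays beyond 2 weeks (section 3.1.3) limits long delays, but it can itself bring early stopping.

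Finally, this is a condensed article, and Table 1 is not shown and may fix more. That is fair for windows and dating rules. The minimum-only wording, however, is stated in the article, and no later analysis plan can make scan dates equal once the data are collected.

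**Conclusion.** The concern holds as a conditional one. The stated schedule permits unequal examination and ties it to a date that may differ by arm, so PFS can be biased. It does not establish that PFS will be. Under assumed medians of 8 to 18 months, the spurious hazard ratio is 0.90 to 0.92 in the extreme scanning contrast, about 0.95 if half of progressions surface between scans, and 0.96 to 0.97 if 30% of one arm ends treatment 8 weeks early (0.91 to 0.93 at 60%). The false-positive rate rises to at most about 8% against a nominal 5%. The 30% and 60% are illustrations: the completion figures in the Introduction concern 5-FU/cisplatin, not S-1 with cisplatin. The primary endpoint and the total of 88 are unaffected. The effect is modest and falls on a secondary endpoint, but it is cheap to prevent and cannot be repaired afterwards.

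**What to change.** 1. Keep the first follow-up CT and endoscopy tied to the primary endpoint's time point. State which date counts as treatment end, and reconcile it with the week-15 response assessment.
2. For later examinations, replace the minimum with one fixed interval, identical in both arms, at the existing minimum frequency. Set it in weeks from randomization with a visit window, and state that it does not move with treatment delay or stopping.
3. Report CT and endoscopy counts per patient-year by arm.
4. Add a PFS sensitivity analysis that dates progression found between examinations to the next scheduled one.
5. If Table 1 already fixes the schedule, align the list with it.

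The cost is a wording change and one extra analysis, and no scans are added for a patient treated to plan. Sites lose some flexibility. The gap between the first and second examination shortens after delayed treatment and lengthens after early stopping (by 8 weeks for a patient who stops 8 weeks early), so the first common date must be chosen with the 6-month limit in mind. A small dependence on treatment end remains at the first examination, because the primary endpoint needs it there; the simulations do not size that remainder.

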### Statistical analysis and randomization

3.6

At a bilateral test 0.05 significance level and a power of 85%, with a dropout rate for each group of 10%, observe 40% endoscopic CR, and to exclude a lower limit of confidence interval (CI) of 20% CR, the study requires a total of 88 samples. Randomization will be administered centrally by the SPSS. Patients who meet the inclusion criteria will be randomized on a 1:1 basis to one of the 2 groups.

The proportion of patients with a clinical response and their 95% confidence intervals will be calculated and reported. The number and proportion of specific cases will be analyzed. The Chi-square test and Kaplan–Meier method will be used to analyze the rates and severity of disease progression and overall survival rate, respectively, according to NCI-CTCAE (version 4), and a Fisher exact (probability) test will be used to analyze the correlations between clinical outcomes and toxicity.

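### Section 3.6: two-sided 0.05, 85% power and 88 patients do not all hold under exact inference; 88 comes from a rule with about 4.3% upper-tail error, whose method and sidedness need stating

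*Protocol article*

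**What the plan says.** Everything on this point is in section 3.6 (Statistical analysis and randomization) of the protocol article.

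- Level, power and dropout: "At a bilateral test 0.05 significance level and a power of 85%, with a dropout rate for each group of 10" per cent.
- Rates: "observe 40% endoscopic CR" is the expected result, and the aim is "to exclude a lower limit of confidence interval (CI) of 20% CR".
- Size: "the study requires a total of 88 samples", randomised 1:1, so 44 per arm.
- Reporting: "The proportion of patients with a clinical response and their 95% confidence intervals will be calculated and reported".

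The section does not say which test or type of interval produced the 88, and it gives no responder cut-off. Section 3.4 says a final statistical plan will be completed and applied to the locked data.

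**The concern.** A two-sided 0.05 test and a 95% interval whose lower limit must lie above 20% both nominally leave 2.5% in the upper tail, the only tail that matters for showing CR above 20%. With about 40 evaluable patients per arm, that tail probability and 85% power cannot both be had under exact binomial inference. The usual two-sided formula also asks for more than 88.

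The 88 can be reached, but by rules whose true chance of wrongly excluding 20% is about 4.3%. A reader who takes the level and power at face value is misled about one of the two. There is also a plausible result, 13 responders of 40, for which the statement that an arm excludes 20% depends on a choice the section does not fix.

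**Working it through.** **Inputs (section 3.6).** p0 = 0.20, p1 = 0.40, two-sided α = 0.05, power 0.85, dropout 10%, total 88. I read the calculation as one-sample, per arm, then doubled. Evaluable per arm: 44 × 0.9 = 39.6, or 40 if the inflation was 40 × 1.1 = 44.

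**Step 1. Reproduce 88.** Three routes work:

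- *One-sided 5%, exact binomial.* The smallest n with at least 85% power is 40, cut-off 13. P(X ≥ 13 | 0.20) = 0.0432; P(X ≥ 13 | 0.40) = 0.8715. 40 × 1.1 = 44; 2 × 44 = 88.
- *One-sided 5%, normal formula with continuity correction.* n = 38.8, so 39; 39/0.9 = 43.3, so 44; total 88.
- *Nominal two-sided 95% Wilson (score) interval with lower limit above 20%.* The first n with at least 85% power is again 40, cut-off 13, power 0.8715; 40 × 1.1 = 44; total 88. At 13/40 the score statistic is (0.325 − 0.20)/√(0.16/40) = 1.976, just above 1.960.

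**Step 2. Normal formula at the stated two-sided level.**

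n = [z₀.₉₇₅√(p0(1−p0)) + z₀.₈₅√(p1(1−p1))]² / (p1−p0)²
= [1.960 × 0.400 + 1.036 × 0.490]² / 0.04 = 41.7, so 42.

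42/0.9 = 46.7, so 47 per arm and 94 in total. Power at n = 40:

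Φ{[0.20√40 − 1.960 × 0.400]/0.490} = Φ(0.98) = 83.7%. With all 44 evaluable it is 86.6%.

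**Step 3. Exact binomial with the upper tail held at 2.5%.**

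| Evaluable per arm | Cut-off | Upper-tail error at 20% | Power at 40% |
|---|---|---|---|
| 40 | 14 | 1.9% | 78.9% |
| 44 | 15 | 2.0% | 83.0% |
| 45 | 15 | 2.5% | 85.7% |

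No count from 36 to 44 reaches 85%; the best is 83.0%, at 44. The first that does is 45, and 45/0.9 = 50 per arm, 100 in total.

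**Step 4. True error of the Wilson rule at n = 40.** Upper tail: P(X ≥ 13 | 0.20) = 4.32%. In the lower tail the interval excludes 20% at 3/40 or fewer: P(X ≤ 3 | 0.20) = 2.85%. The total is 7.17%, against a nominal 5%. The power is also specific to n = 40: it is 84.5% at n = 39. At n = 44 the cut-off moves to 15 and power is 83.0%, the same as the exact rule.

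**Step 5. What happens at 13/40 (32.5%).**

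| Interval | Lower limit | Excludes 20%? |
|---|---|---|
| 95% Clopper-Pearson | 18.6% | no |
| 95% Wald | 18.0% | no |
| 95% Wilson | 20.08% | yes |
| 90% Clopper-Pearson (one-sided 5%) | 20.4% | yes |

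The probability of exactly 13/40 is 8.3% in an arm whose true CR rate is 40%.

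**The case against.** The best reply is that the stated inputs do give 88. A nominal two-sided 0.05 score test, equivalent to a 95% Wilson interval, reaches 87.1% power at 40 per arm. The section names no exact method, and attained error that differs from nominal is a familiar feature of approximate methods on discrete data. By the plain normal formula the shortfall at 40 is only 1.3 points (85% − 83.7%), and with all 44 evaluable there is none. The interval type is commonly left to the analysis plan. Section 3.6 uses exclusion of 20% to justify the size and does not set a formal go/no-go rule for each arm.

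Much of this stands. Three stronger readings are tempting and are not supported:

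- *That 88 can only have come from a one-sided test.* The Wilson route gives the same number at a nominal two-sided level.
- *That power at the stated level simply is 79%.* That is the exact figure; at n = 40 it is 78.9%, 83.7% or 87.1% according to method.
- *That 13/40 turns on sidedness alone.* Two 95% intervals, both two-sided, already disagree on it.

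What does not stand is that the Wilson route removes the problem. It meets 85% at n = 40 only by letting the upper-tail error rise to 4.3%, about 1.7 times 2.5% (4.3/2.5), and it falls below 85% at 39 and at 44. Nor is this only detail for the analysis plan: level, sidedness, power, rates and total are all printed in section 3.6, and the issue is whether they agree.

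**Conclusion.** The concern holds in a limited form. Under exact inference the stated level, power and size are not jointly attained: with the upper tail at 2.5%, power is 78.9% at 40 evaluable per arm and at most 83.0% at 44. The 88 is explained by a 13/40 rule with 87.1% power and a true upper-tail error of 4.3% (about 7.2% in total for the two-sided Wilson version). Whether 13/40 excludes 20% depends on both sidedness and interval method.

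This rests on three assumptions: the calculation is one-sample within each arm, about 40 per arm are evaluable, and the true rate is 40%. The first is the reading under which 88 reproduces, though the section does not state it. The point concerns the level of that per-arm criterion; it is not a claim about powering the comparison between arms, and it does not show that more patients must be recruited. It deserves correction because section 3.6 offers these figures as the justification for the trial's size.

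**What to change.** In section 3.6, name the test or interval and the sidedness that produced the 88, and make the printed figures match. One of these would do:

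1. Keep two-sided 0.05 with an exact (Clopper-Pearson) 95% interval, and state power as about 79% with 40 evaluable per arm (cut-off 14/40) or 83% with 44 (cut-off 15/44).
2. If the calculation was one-sided, say one-sided 0.05 and judge exclusion of 20% by the lower limit of a 90% interval (cut-off 13/40, power 87%).
3. If a Wilson or score interval was used, name it, and state that its attained upper-tail error at 40 evaluable is about 4.3%.

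The choice should be recorded before any response data are seen, so that a result such as 13/40 has one reading. The change is about one sentence and no extra patients. The price is a less favourable stated power under option 1, or an openly larger stated error under options 2 and 3.

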## Introduction

1

Esophageal cancer (EC) is a common malignancy worldwide.^[1]^ Squamous cell carcinoma is the most common histological type of EC worldwide, with a higher incidence in developing nations.^[2]^ In China, in 2015, the total incidence and mortality rates of EC were 477.9 and 375.0 per 100,000 persons, respectively, and over 90% of cases are esophageal squamous cell carcinoma.^[3,4]^ The incidence and mortality of EC ranks third in China. Yanting in Mianyang city is one of the highest risk areas for EC in the world.^[5]^

Surgery, radiation therapy, and chemotherapy are the major treatments for EC. But at initial diagnosis, 40% to 60% of patients are not candidates for surgery.^[6]^ In these patients, definitive chemoradiotherapy (CRT) is the established treatment of choice. Early trials have shown beneficial effects of CRT compared to radiotherapy alone,^[7,8]^ and definite CRT has been shown in smaller studies to be comparable in efficacy to surgery in patients with nonmetastatic disease.^[9,10]^ Concomitant use of chemotherapy and a radiation dose schedule that is more efficient compared to conventional radiotherapy may provide better outcomes in patients with EC.^[11]^ The chemotherapeutic drugs cisplatin and 5-fluorouracil have been most commonly used in studies examining the effects of definitive CRT in EC.^[12]^ However, despite many advances in diagnosis and treatment, the 5-year survival rate for patients diagnosed with EC ranges from 15% to 20%.^[12]^

Chemotherapy regimens are often a 2-drug regimen in concurrent chemotherapy and radiotherapy for EC.^[13]^ However, some retrospective studies have suggested that for patients with EC receiving radiotherapy combined with 5-FU/cisplatin chemotherapy, due to severe toxicity, only 9% to 38.5% of patients completed the planned treatment. In addition, one study showed that patients receiving radiotherapy combined with 5-FU/CDDP chemotherapy experienced a treatment-related mortality as high as 18%.^[7,14–17]^ Therefore, it is necessary to explore the toxicity of the combined program to improve its treatment tolerance and safety.

In recent years, S-1 reflects the good effect, single use or combined with platinum or combined with radiotherapy have achieved good results, especially the S-1 alone with the combination of radiotherapy treatment effect is very good, and achieved good clinical remission rate (CR).^[18–22]^

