#### Drop-out criteria

3.1.3

Criteria that will lead to the drop-out of a patient before completion of this study may be any kind of treatment for medical reasons or impairment that will result in an interruption or early completion of treatment, include:

1.The withdrawal of the informed consent of patients.2.Patient safety events.3.Chemotherapy delays because of toxicity lasting for more than 2 weeks.4.The patient enrolled in another study during the clinical study.5.Patient does not want to continue to participate.6.The compliance of the patient is not sufficient.7.The researchers’ judgment.

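### The equal 10% dropout behind the 88 patients has no stated source and is hard to reconcile with a drop-out definition that includes stopping or interrupting treatment

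*Protocol article*

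**What the plan says.** Four parts of the protocol article bear on this point.

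- **Section 3.6** gives the sample size: "At a bilateral test 0.05 significance level and a power of 85" per cent, "with a dropout rate for each group of 10" per cent, a target stated as "observe 40% endoscopic CR", the aim "to exclude a lower limit of confidence interval (CI) of 20% CR", and the result "the study requires a total of 88 samples". Patients are "randomized on a 1:1 basis to one of the 2 groups", so 44 per arm. No source is given for the 10%, and the same rate applies to both arms.
- **Section 3.1.3** defines drop-out before the end of the study through treatment events, among them "impairment that will result in an interruption or early completion of treatment". Its list includes safety events, chemotherapy delayed by toxicity for more than 2 weeks, and insufficient compliance.
- **Section 1 (Introduction)** reports, from retrospective series of radiotherapy with 5-FU/cisplatin, that "due to severe toxicity, only 9% to 38.5% of patients completed the planned treatment". The Abstract and section 4 extend the toxicity concern to two-drug regimens in general, without figures. Section 4 expects fewer side effects with S-1 alone.
- **Section 3.5** plans intention-to-treat analysis for all the other endpoints. It does not name the analysis population for the primary endpoint, endoscopic CR 3 months after treatment.

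**The concern.** The trial is motivated by the poor tolerability of two-drug chemoradiotherapy. Its control arm is a two-drug regimen, and section 3.1.3 turns treatment intolerance into drop-out from the study. Read together, these suggest that drop-out in the control arm may exceed 10% and may exceed drop-out in the S-1 arm. Section 3.6 assumes neither.

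Two things are at stake. The first is precision: if drop-outs have no response assessment, the control arm has fewer evaluable patients than the calculation needs. The second is comparability: loss that is driven by toxicity and unequal between arms leaves a control group selected for tolerance. The more correct the trial's premise is, the greater both problems become.

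**Working it through.** **Inputs.** From section 3.6: CR rate 40%, rate to exclude 20%, power 85%, drop-out 10%, total 88, allocation 1:1. From the Introduction: completion 9% to 38.5% for 5-FU/cisplatin. The drop-out rates of 30% and 50% used below are assumptions, because the document gives no rate for S-1/cisplatin.

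**Step 1: the plan's own figure.** Treat each arm as an exact one-sample binomial test of 20% against 40% at one-sided 0.05. The smallest n with at least 85% power is 40: declare success at 13 or more responders, with actual error 0.043 and power 0.871. Then 40 × 1.1 = 44 per arm, and 2 × 44 = 88. Dividing by 0.9 instead gives 40/0.9 = 44.4, so 45 per arm and 90 in total. In the other direction, 44 × 0.9 = 39.6. The plan therefore rests on about 40 evaluable patients per arm. (The stated two-sided 0.05 does not give 88 by the same exact method: 0.025 per tail needs 45 evaluable, so 50 per arm and 100 in total. That is a separate matter.)

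**Step 2: what fewer evaluable patients would do.** For each n, find the smallest number of responders x whose two-sided 95% lower limit exceeds 20%. Then compute P(X ≥ x) for X ~ Bin(n, 0.40). Evaluable n = 44 × (1 − drop-out), rounded.

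| Drop-out | Evaluable n | x, exact / Wilson | Probability, exact / Wilson |
|---|---|---|---|
| 10% (plan) | 39.6, so 40 | 14 / 13 | 79% / 87% |
| 30% (assumed) | 30.8, so 31 | 12 / 11 | 62% / 75% |
| 50% (assumed) | 22 | 9 / 9 | 55% / 55% |

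All rows assume that every drop-out lacks a response assessment and that CR among those assessed is still 40%.

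**Step 3: if drop-outs count as non-responders instead.** Keep all 44 in the denominator and assume 40% CR among the rest. Success then needs 15 responders by either interval. At 10% drop-out the overall CR rate is 0.9 × 0.40 = 36% and P(X ≥ 15) is about 66%. At 30% it is 0.7 × 0.40 = 28% and about 23%. The assumed rate therefore matters under this handling too.

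**Step 4: the cited figures.** Completion of 9% to 38.5% means that 61.5% to 91% did not complete. These are shown only to explain the tension. They describe another regimen and are not used as a forecast for the control arm.

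**The case against.** A reader might infer that the protocol contradicts itself outright: that 61.5% to 91% of control patients will drop out and that the arm cannot deliver its planned number. The document does not support that, for four reasons.

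- The completion figures come from retrospective 5-FU/cisplatin series. The control regimen is S-1 plus cisplatin, for which no completion rate is given, and the Introduction speaks well of S-1 combined with platinum.
- Failing to complete planned treatment, which the Introduction does not define, need not equal drop-out under section 3.1.3. The toxicity item there covers only delays over 2 weeks.
- A patient who stops treatment can still have the 3-month endoscopy. The follow-up schedule in section 3.5 does not limit endoscopy and CT to those who completed treatment, and nothing says that drop-outs leave the CR count.
- The 30% and 50% rates have no source in the document. The starting point also depends on the interval: by the exact method the plan is already at 79% with 10% drop-out.

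All four stand, and they rule out the stronger reading. They do not remove the narrower one. The opening words of section 3.1.3 do overlap with non-completion of treatment, the patients concerned are described as dropping out of the study, and intention-to-treat is promised only for the other endpoints. The text shown does not keep these patients in the primary analysis. The full protocol or analysis plan may name the primary population, but the 10% is a stated input and should agree with the stated definition of drop-out.

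**Conclusion.** The point holds as a problem of justification and consistency. It does not show that the trial must fail. The equal 10% is unsourced, and it is hard to square with a drop-out definition tied to treatment and with the expectation that the two-drug arm is less well tolerated.

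The size is conditional. If drop-outs go unassessed, an assumed 30% in the control arm lowers the chance of excluding 20% by 17 points with the exact interval (79% to 62%) or 12 points with Wilson (87% to 75%). An assumed 50% lowers it to 55% with either. If all patients are assessed whether or not they complete treatment, this loss of evaluable patients does not arise. The true drop-out rate on S-1/cisplatin cannot be read from the document. The change is worth making because it is cheap and guards against both a shortfall and unequal loss.

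**What to change.** 1. Reconcile the Introduction, section 3.1.3 and section 3.6 so that the rationale, the definition of drop-out and the assumed rate agree.
2. In section 3.1.3, state that a patient who stops or interrupts treatment stays in the study and has the planned 3-month endoscopy and CT, unless consent to follow-up is withdrawn. This concerns data collection only and changes no rule for stopping treatment.
3. In section 3.6, define the 10% as patients with no response assessment.
4. If drop-out is to stay tied to treatment completion, justify a rate for each arm and restate the power that 88 patients give over a range of rates. The rates in the table above illustrate sensitivity and should not be adopted as planning values.

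The cost is wording in two sections. No patients are added, and no procedures beyond visits already scheduled. The downside arises only under item 4, where the stated power may be less favourable.
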